### Ethical Considerations

The study procedures were approved by the Biomedical Research Alliance of New York Internal Review Board (Pilot RCT: FQHC Intervention for Uptake of CGM in Hispanic Adults With T1D, 24-08-011-910). Consistent with best practices in research, informed consent will be collected from the person with diabetes and the family member, and they can opt out at any time. All data will be deidentified to protect the privacy of participants. Intervention participants will be compensated following each study activity with a total amount of US $100 at baseline and up to US $900 (intervention participants with T1D) or US $500 (friend or family member of intervention participants with T1D) at 3 months after baseline. Intervention participants with T1D will be compensated up to US $700 at 6 months after baseline. In addition, control participants will be compensated following each study activity with a total amount of US $100 at baseline and up to US $550 at 3 months after baseline and US $600 at 6 months after baseline.

### Data Analytic Plan

#### Study Aim 1

Three aspects of study feasibility will be evaluated using a combination of univariate and bivariate statistical methods. Recruitment sources along with rates and levels of participant retention will be quantified relative to sites and time. Qualitative data on the rationale for study refusal, with the use of data coding, will be quantified. Participant characteristics (eg, age, gender, country of origin, and time since T1D diagnosis) will be summarized using means and SDs or frequencies and percentages, as appropriate to the level of measurement. Associations between participant characteristics and dropout frequency will be investigated via cross-tabulations. Retention will be assessed by participant adherence to the study schedule (Figures 3 and 4). Rates and patterns of adherence to intervention and control procedures and attendance throughout the study duration will be described. Acceptability of the intervention among FQHC providers, CDCES, and intervention participants will be appraised through content analysis of posttrial FGIs [83], using Graneheim and Lundman [84] qualitative content analysis approach to increase trustworthiness. This coding approach involves reading the FGIs several times and identifying and condensing meaning units that are words, sentences, or paragraphs containing aspects related to each other through their content and context. Next, the condensed text will be abstracted with codes, categories, and themes to best represent the perspectives of FQHC providers, CDCES, and intervention participants, respectively.

Completeness and validity of data collection procedures will be assessed by documenting the frequency of missing data and by checking for inconsistent or out-of-range values for all study variables. In-text data on barriers to data collection will be analyzed qualitatively using content analysis [83]. Successful implementation of study procedures will be evaluated via debriefing of study staff and documentation of any departures from the study protocol.

#### Study Aim 2

To quantify intervention signals, we will begin by contrasting HbA_1c_ levels between the intervention and control participants. To do this, we will apply linear mixed modeling (LMM) using study arm assignment (intervention vs control) and time (3 and 6 months) as “main effects,” the corresponding baseline value of HbA_1c_ as a covariate, and FQHC site variable as well as the “participant” identifier as random effects. This approach will support statistical testing of intervention effects on the mean value of HbA_1c_ while controlling for differences in baseline levels of the variable, accounting for clustering effects with study sites, and adjusting for correlations within participants over time. After using this strategy to assess the main effect of the intervention on the mean value of HbA_1c_, we will investigate the possibility of “intervention-by-time” and “intervention-by-site” interactions and the possibility that any imbalances in baseline participant characteristics (sociodemographic variables and health history factors) between study groups might confound valid estimation of intervention effects. Because the RCT is primarily concerned with feasibility assessment and will involve small samples with limited statistical power, the focus of these analyses will be “effect estimation” rather than formal statistical testing. In the second stage of analysis, we will apply the same modeling strategy to contrast the other physiological outcomes and the psychosocial measures between the intervention and control participants.

Throughout our analyses using LMM, we will attempt to respond to evidence of nonnormality in any of the outcome measures by applying normalizing transformations. If no transformation achieves approximate normality (as is likely to be the case for the time in range, below range, and above range variables as well as the counts of hypo- and hyperglycemic clinical events), we will, instead, apply a generalized linear mixed model with a link function appropriate to the distribution of the outcome measure. Mixed models of repeated measures are robust to the effects of missing observations that occur “at random.” Depending on the extent of missing data (while acknowledging restrictions imposed by the study’s small sample size), sensitivity analyses based on multiple imputations may be conducted to evaluate the potential impact of nonrandom missing data on estimates of the intervention effects.

For members of the intervention arm of the RCT, participant “dose” of the intervention will be described with a combination of means or SDs and frequencies or percentages. Additional analyses using LMM methods will be conducted to evaluate whether measures of intervention dose are associated with differential mean levels of the physiological and psychosocial outcome variables at the 3- and 6-month time points. Finally, we use results of LMM analyses for the following: (1) to calculate standardized effect sizes (Cohen *d* and eta-squared) for the intervention versus control condition on each of the physiological and psychosocial outcome measures, (2) to determine variance estimates for these outcome variables, (3) to quantify clustering effects (in the form of intraclass correlation coefficients) introduced by the study sites, and (4) to document temporal correlations of outcome measures within participants across the 3 study time points (baseline, 3 months, and 6 months). These statistics will be helpful, but not fully definitive (due to the small sample size), in guiding design decisions and statistical power analyses in preparation for a future, full-scale RCT of the CGM intervention.

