**Methods:**

A mixed methods, pragmatic pilot RCT will be used. A total of 30 adult Hispanic patients with T1D will be recruited from 4 FQHC sites allocated to provide the intervention (n=2) or control (n=2) conditions. At intervention sites, participants must be willing to use CGM for 3 months and have a willing adult family member participate in the study. Guided by the socioecological model, our intervention has three levels: (1) individual (culturally sensitive CGM information, motivation, and skills acquisition), (2) family or social networks (integration of the core Hispanic values of *familismo* and *collectivismo* to leverage family and peer support for CGM uptake), and (3) health care provider levels with CGM training using Project ECHO (Extension for Community Healthcare Outcomes). Intervention participants (n=15) will receive a culturally sensitive CGM intervention with 4 weekly intervention sessions (coattended by a family member), followed by 7 peer support group sessions over 6 months. Control participants will receive a self-monitoring of blood glucose control condition over a 6-month period. Study feasibility will be assessed in terms of recruitment, enrollment, retention, adherence, study procedures and implementation, and acceptability with mixed methods. We will collect physiological (eg, glycated hemoglobin and CGM metrics) and psychosocial (eg, depression, quality of life, social support, and interpersonal processes of care) outcome data. Feasibility data will be analyzed using content analysis and univariate or bivariate statistics. Linear and generalized linear mixed modeling will assess intervention signals and clinically meaningful differences from baseline to 3 and 6 months.

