### Study Aims

The aims of the study are as follows:

Assess study feasibility: (a) recruitment yield by type and retention (differential rates by participant characteristics), (b) retention, (c) implementation (data collection procedures, intervention fidelity, and dosages), and (d) acceptability.Assess or estimate (a) significant intervention signals from baseline to 3 and 6 months (physiological and psychosocial outcomes), (b) relationship of dose to outcomes, and (c) clinically meaningful differences in T1D outcomes.

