## Methods

### Study Design and Sampling

A mixed methods, pragmatic pilot RCT will be used to evaluate the study’s aims. Mixed methods will be used to assess study feasibility and acceptability, while quantitative methods will be used to assess RCT outcomes.

We randomized 4 Connecticut FQHC sites to serve as control (n=2) or intervention (n=2) sites. Inclusion and exclusion criteria are listed in Table 1. We plan to enroll 15 intervention and 15 control participants. Our sampling goal reflects that the RCT is primarily focused on the assessment of feasibility rather than intervention efficacy, as there is a lack of CGM intervention studies for Hispanic adults with T1D at FQHC. Therefore, the pilot study will test key aspects of the study design, such as recruitment strategies, data collection methods, intervention protocols, and participant engagement, before conducting a full-scale RCT. The total sample size of 30 will support the estimation of the proportions of participants who have “satisfactory” feasibility measures with SEs that cannot exceed ±0.1. Additionally, the “per group” sample sizes (15 a piece) will support the estimation of variances for outcome variables with sufficient precision to guide power analyses for a subsequent, full-scale RCT.

**Table 1 table1:** Inclusion and exclusion criteria.

			Potentially eligible intervention participants		Potentially eligible control participants

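### Cross-tabulation is the only method named for relating participant characteristics to dropout, although age and time since diagnosis are continuous; compare those on their own scale (minor)

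*Protocol article*

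**What the plan says.** The Study Aims section lists, under feasibility, "retention (differential rates by participant characteristics", and Textbox 2 repeats differential retention by characteristics as a measure of the primary feasibility outcome. The sample is fixed: "We plan to enroll 15 intervention and 15 control participants".

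In the Data Analytic Plan, Study Aim 1 opens with "Three aspects of study feasibility will be evaluated using a combination of univariate and bivariate statistical methods". It then says "Participant characteristics (eg, age, gender, country of origin, and time since T1D diagnosis) will be summarized using means and SDs or frequencies and percentages", with the choice of summary following the level of measurement. On dropout it says "Associations between participant characteristics and dropout frequency will be investigated via cross-tabulations". The section gives no cut points, test, significance level or expected number of dropouts for that step, and names no comparison of continuous characteristics on their own scale.

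**The concern.** The plan respects the level of measurement when it summarises characteristics, but not when it relates them to dropout. Gender and country of origin fit a table. Age and time since diagnosis do so only after being cut, and so would time living in the United States, which Table 4 records at baseline.

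With 30 people and a handful of dropouts, a cut table has cells of 0 to 5 on the dropout side. Its message can change with the cut point, and it ignores how far above or below the cut each person lies. At stake is a modest but real purpose of the pilot: learning who is lost, so that retention can be planned for the full-scale trial.

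**Working it through.** **Inputs from the protocol article.** N = 30, 15 per arm (Study Design and Sampling). Method: cross-tabulation (Study Aim 1). Only precision figure: "feasibility measures with SEs that cannot exceed ±0.1".

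**Inputs not in the article, assumed here.** Two-sided 5% level; 3 to 10 dropouts; a normally distributed characteristic with equal SDs; dropouts and completers differing by d SDs (main case d = 1.0); a cut at the pooled median, so 15 people on each side.

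**Step 1: the plan's own figure.** The largest SE of a proportion at N = 30 is √(0.25/30) = 0.091, below 0.1, so the stated bound reproduces. It concerns the whole sample. For a retention rate within one half of a median split the largest SE is √(0.25/15) = 0.129.

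**Step 2: what a median-split table can show at all.** This needs no assumed effect size. If all k dropouts fall on one side of a 15/15 split, the two-sided Fisher p-value is 2·C(15,k)/C(30,k):

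- k = 3: 2 × 455/4060 = 0.22
- k = 4: 2 × 1365/27405 = 0.10
- k = 5: 2 × 3003/142506 = 0.042
- k = 6: 2 × 5005/593775 = 0.017; a 5-to-1 split already gives 0.17

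So with fewer than 5 dropouts (retention above 25/30 = 83%) Fisher's test cannot reach 5% however strong the association. With 5 or 6 it does so only if every dropout is on the same side.

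The uncorrected chi-square is slightly less restrictive. For 3 dropouts on one side it is 30 × (3 × 15)²/(15 × 15 × 3 × 27) = 3.33, p = 0.07. For 4 it is 30 × (4 × 15)²/(15 × 15 × 4 × 26) = 4.62, p = 0.03, but with expected dropout cells of only 2.

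**Step 3: illustrative power at d = 1.0.** Simulation with 100,000 replicates per row (Monte Carlo SE below 0.2 points); differences taken before rounding.

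| Dropouts | t-test at 5% | Exact rank-sum | Fisher, median split | Rank-sum minus Fisher |
|---|---|---|---|---|
| 5 | 50.7% | 47.1% | 31.6% | 15.5 |
| 6 | 56.1% | 50.5% | 22.6% | 27.9 |
| 8 | 64.7% | 59.8% | 41.0% | 18.8 |
| 10 | 70.1% | 67.1% | 20.5% | 46.6 |

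**Step 4: separate the cut from Fisher's conservatism.** On a 15/15 split, Fisher's test at nominal 5% has an actual size of 4.2%, 1.7%, 3.5% and 0.5% for 5, 6, 8 and 10 dropouts. Run at those same sizes, the t-test has 47.6%, 37.8%, 58.6% and 34.4% power. The size-matched loss is then 15.9, 15.2, 17.6 and 13.9 points, so about 14 to 18.

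**Step 5: how far the figure moves.** Losses below are against a t-test at 5%, from 4,000 replicates per setting.

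- Tertiles with chi-square, 3 or 5 dropouts, d = 0.5: no loss (−0.8 and −1.6 points, within or near simulation error).
- Median split with uncorrected chi-square, 10 dropouts, d = 2.0: 1.7 points.
- Median split with Fisher, 10 dropouts, d = 1.2: 51 points.
- Median split, 3 dropouts, d = 1.5: 68 points, which is all of the t-test's power.

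**Step 6: what the original scale would deliver.** The half-width of a 95% interval for the mean difference, in SD units, is t(28 df) × √(1/k + 1/(30−k)), with t = 2.048. For k = 5 it is 2.048 × √(0.200 + 0.040) = 1.00. For k = 8 it is 2.048 × √(0.125 + 0.045) = 0.85. The intervals are wide, but they show how uncertain the answer is and depend on no cut point.

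**The case against.** The strongest reply is that nothing is being tested. Aim 1 is descriptive, the sample size is justified by standard errors of proportions, and for Aim 2 the plan concedes that the trial "will involve small samples with limited statistical power". No stated target is therefore missed. This stands: power is only a yardstick here. It does not rescue the cut, because unstated cut points and tiny cells make a poor description too.

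Second, a differential retention rate is a rate within groups, which is naturally a table. This is fair for gender and country of origin. For age or years since diagnosis it holds only after a choice of groups that the plan does not make.

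Third, a condensed article may leave grouping details, or a companion comparison of means, to an analysis plan. Cut points could well sit there. But the article does name a method for all characteristics, and that method does not suit some of its own examples.

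Fourth, the continuous comparison is weak as well. With 5 to 10 dropouts the t-test has about 17% to 24% power at d = 0.5 and 35% to 51% at d = 0.8. This stands, and it limits what the change can achieve.

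A reader might also infer that this analysis chooses covariates for the Aim 2 mixed models. The article does not say so. Aim 2 names baseline HbA1c as the covariate and looks at baseline imbalance between study groups, not at predictors of dropout.

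**Conclusion.** The point holds as a minor one. The only stated method for linking characteristics to dropout forces continuous characteristics into categories, for a listed measure of the primary feasibility outcome, in a sample too small to spare the information.

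It would be tempting to quote one power loss as a property of this 30-person trial. The document does not support that: test, level, cut, dropout count and effect size are all assumed. At a 1-SD difference with a median split and 5 to 8 dropouts, the gap between rank-sum and Fisher is about 15 to 28 points, and the size-matched loss against a t-test is about 14 to 18. Elsewhere it ranges from near 0 to over 50. The result that needs no assumed effect is that, with fewer than 5 dropouts, a two-sided Fisher test on a median split cannot reach 5%.

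No between-arm estimate is affected.

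**What to change.** Amend the one sentence in Study Aim 1. Keep cross-tabulations for categorical characteristics such as gender, country of origin and language preference. For continuous ones (age, time since T1D diagnosis and, where it applies, time living in the United States), compare dropouts with completers on the original scale. Report either a difference in means or medians with a 95% confidence interval, using a rank-based or exact method where dropouts are few, or a penalised (Firth) logistic regression with one covariate at a time. Present the results as estimates, in line with the emphasis the plan already adopts for Aim 2.

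If grouped retention rates are also wanted, state the cut points in advance and show them beside the continuous comparison.

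The cost is one sentence and a few lines of code. The variables are already collected at baseline.

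### With two whole sites per arm, the planned intervention-by-site interaction cannot be estimated, and the arm effect and the site ICC both rest on 2 degrees of freedom

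*Protocol article*

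**What the plan says.** Study Design and Sampling states the design: "We randomized 4 Connecticut FQHC sites to serve as control (n=2) or intervention (n=2) sites". The abstract agrees, with participants "recruited from 4 FQHC sites allocated to provide the intervention (n=2) or control (n=2) conditions". The enrolment target is given as "We plan to enroll 15 intervention and 15 control participants".

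The Data Analytic Plan, Study Aim 2, fits a linear mixed model for HbA1c. Arm and time are main effects, baseline HbA1c is a covariate, and site and participant are random effects. The model is said to support testing of the intervention effect while "accounting for clustering effects with study sites, and adjusting for correlations within participants over time". The plan then undertakes to "investigate the possibility of “intervention-by-time” and “intervention-by-site” interactions". The same modelling strategy is to be applied to the other outcomes. One listed use of the results is "to quantify clustering effects (in the form of intraclass correlation coefficients) introduced by the study sites", to help plan the full-scale trial.

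Two caveats are given. The focus is on estimating effects rather than on formal testing, and the derived statistics are described as useful but not definitive. Both caveats are attributed to small samples. Neither mentions the number of sites or the nesting of site within arm.

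**The concern.** An intervention-by-site interaction asks whether the effect of the intervention differs from site to site. That requires sites in which both conditions are observed, and here there are none. The stated design therefore cannot support the stated analysis, and no detail in a separate analysis plan could rescue it. Software would drop the term, return an error or print something with no meaning.

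The same nesting governs the rest of the model. The intervention is compared between sites, so the information on the arm effect and on the site ICC is limited by four sites, not by 30 people. If the site variance is estimated as zero, the fitted model treats participants as independent and the intended adjustment disappears. If the ICC is reported without its interval, the designers of the full-scale trial could read a zero as absence of clustering.

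**Working it through.** **Inputs from the protocol.** 4 sites, 2 per arm, one condition per site; 15 participants per arm, so 30/4 = 7.5 per site on average.

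**Assumptions.** The protocol gives no ICC, so a range is shown. Other assumptions are a two-sided 5% level, balanced sites, one follow-up time and no baseline covariate.

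**The plan's own figure.** The sample-size paragraph promises "feasibility measures with SEs that cannot exceed ±0.1". For a proportion of 0.5, √(0.25/30) = 0.091, so the figure reproduces under independence. It is the only numerical justification given, and it does not bear on the model discussed here.

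**Interaction.** A full crossing of 2 arms and 4 sites has 8 cells, and the interaction would have (2−1)×(4−1) = 3 df. Only 4 cells exist. They carry 3 df: 1 for arm and 2 for sites within arm. Nothing is left for the interaction. The rank of the design matrix confirms this:
- site alone: 4
- site + arm: 4
- site + arm + arm-by-site: 4

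Declaring the term as a random slope does not help. Arm is constant within a site, so such a slope can only appear as a different site variance in each arm, on 1 df each. Intervention-by-time is unaffected and remains estimable.

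**Arm effect.** Between-site df = 4 sites − 2 arms = 2. The critical value is t(2) = 4.30, against 2.05 on 28 df. There are C(4,2) = 6 possible allocations, so the smallest two-sided site-level randomization p-value is 2/6 = 0.33.

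In SD units, SE of the arm difference = √[2 × (ICC/2 + (1−ICC)/15)]. At ICC 0.05 this is √[2 × (0.025 + 0.0633)] = 0.420.

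| ICC | SE | half-width, 4.30 × SE | half-width, 1.96 × SE |
|---|---|---|---|
| 0 | 0.365 | 1.57 | 0.72 |
| 0.01 | 0.377 | 1.62 | 0.74 |
| 0.05 | 0.420 | 1.81 | 0.82 |
| 0.10 | 0.469 | 2.02 | 0.92 |

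**Behaviour under the null** (1,000,000 draws; between-site mean square on 2 df, within-site on 26 df, pooled to 28 df when the site variance is estimated as zero). The Satterthwaite-type rule uses t on 2 df when the site variance is positive and on 28 df when it is zero.

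| ICC | site variance estimated as 0 | error, normal reference | error, Satterthwaite-type df | error, site-level t on 2 df |
|---|---|---|---|---|
| 0.01 | 59% | 5.1% | 3.4% | 5.0% |
| 0.05 | 50% | 7.1% | 4.6% | 5.0% |
| 0.10 | 41% | 9.3% | 5.7% | 5.0% |

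**ICC.** For an observed ICC of 0.05 with 7.5 per site, F = 1 + 7.5 × 0.05/0.95 = 1.395 on 2 and 26 df. The F quantiles are 4.265 (upper 2.5%) and 0.0253 (lower 2.5%).
- Lower limit: 1.395/4.265 = 0.327, and (0.327 − 1)/(0.327 + 6.5) = −0.10, in effect 0.
- Upper limit: 1.395/0.02534 = 55.0, and (55.0 − 1)/(55.0 + 6.5) = 0.88.

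**The case against.** The aliasing of the interaction is not open to dispute. The case on the other side concerns the rest.

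- **A reader might infer that the model cannot deliver a clustering-adjusted test at all.** The documents do not support that. The model can be fitted, an ICC can be computed and a valid 2-df test exists. Inflated error arises only if the statistic is referred to a normal distribution. The protocol names no reference distribution, and that choice may properly sit in an analysis plan that is not shown. With Satterthwaite-type df the error stays at about 3% to 6% over ICC 0.01 to 0.10.
- **A reader might infer that intervals will usually be too narrow.** That depends on an ICC the protocol does not give. The estimated SE falls below the true SE in 44% of simulated trials at ICC 0.01, 50% at 0.02 and 59% at 0.05.
- **A reader might infer that the plan overlooks site randomization throughout.** It does not. Site randomization is stated and site is fitted as a random effect; only the interaction clause ignores the nesting.
- **A reader might set Aim 2(a), which seeks "significant intervention signals from baseline to 3 and 6 months", against the emphasis on estimation.** That is a matter of wording, because the analysis section already says estimation governs.
- **A reader might predict that the full-scale trial will ignore clustering.** No passage says so, and which ICC that trial should use is outside this protocol.

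The caveats on estimation and on non-definitive statistics are real and lower the severity. They do not answer the point, because they name sample size as the cause. More participants at the same four sites would leave the interaction inestimable and the arm effect on 2 df.

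**Conclusion.** The intervention-by-site analysis is wrong as written. It follows from the allocation alone, needs no assumption, and holds at any number of participants.

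The arm contrast and the site ICC can be computed, but each has only 2 df behind it. A 2-df interval for the arm difference has a half-width of roughly 1.6 to 2.0 SD over ICC 0 to 0.10. The site variance is estimated as zero in about half of trials at a true ICC of 0.05, and an observed ICC of 0.05 is compatible with almost anything from 0 to 0.88. These figures rest on the assumed ICCs and on a simplified balanced model with one time point and no baseline covariate. The 2 df do not depend on the assumed ICC.

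Severity is should-fix. The primary outcome is feasibility, and the affected analyses are secondary and already described as estimation.

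**What to change.** 1. Delete the intervention-by-site interaction from Study Aim 2. In its place, show the four site-specific baseline-adjusted means and the between-site difference within each arm. Keep intervention-by-time.
2. Report the arm effect with an interval from site-level summaries on t with 2 df. This does not mean multiplying a REML standard error by 4.30 when the site variance is estimated as zero: that combination is far too conservative, with an error of about 0.06% at ICC 0.05.
3. State that the imprecision of the arm effect and of the ICC comes from having two sites per arm, not only from the small sample.
4. Report each site ICC with its interval, so that a zero estimate is not read as absence of clustering.

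These are changes of analysis wording only, with no effect on recruitment or conduct. The downside is wider reported intervals, which reflect the precision that four sites can give.

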#### Secondary Outcomes

Physiological outcomes are HbA_1c_, time in range, time below range, time above range, and frequency of hypoglycemic- or hyperglycemic-related ED visits or hospitalizations (Textbox 1). HbA_1c_ will be measured with the DCA 2000 point-of-care analyzer with a capillary blood sample, the standard measure of HbA_1c_ determination at the study FQHC. CGM glycemic metrics will be captured from FreeStyle Libre View reports (intervention participants only). The frequency of hypoglycemic- or hyperglycemic-related ED visits or hospitalizations over the past 3 months will be based on participant self-report (Textbox 1).

Psychosocial outcomes are depression, quality of life (QOL), social support, and interpersonal processes of care. All psychosocial measures are available in English and Spanish. Depression will be assessed with the 2-item Patient Health Questionnaire (PHQ) and 9-item PHQ. The PHQ-2 is a screening tool for depression. The PHQ-2, using the first 2 items of the PHQ-9, inquires about depressed mood and anhedonia over the past 2 weeks with item scores ranging from 0=not at all to 3=nearly every day. A total PHQ-2 score of >3 suggests major depressive disorder and warrants administration of the PHQ-9 [77]. PHQ-9 item scores likewise range from 0 to 3 (maximum score of 27). A threshold score of >10 indicates mild major depression, >15 or higher indicates moderate major depression, and >20 indicates severe major depression [78].

QOL will be measured by the Medical Outcomes Survey Short Form-36. This well-validated and reliable measure has 8 sections to capture distinct domains of QOL. Each section yields a scored scale, which is a weighted sum of the items in each section. Pooled scores are calculated to generate a total score, ranging from 0 to 100, with lower and higher scores indicating less or greater health-related QOL, respectively (Textbox 1) [77-79].

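### Between-arm Cohen d and eta-squared are promised for every outcome, but cannot be computed for the three CGM range metrics and do not fit the four event counts

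*Protocol article*

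**What the plan says.** The Secondary Outcomes section lists the physiological outcomes as HbA1c, "time in range, time below range, time above range, and frequency of hypoglycemic- or hyperglycemic-related ED visits or hospitalizations". Table 4 splits the last item into four counts: ED visits and hospitalizations, each for hypoglycemia and for hyperglycemia. Both Table 4 and the Secondary Outcomes section restrict the CGM metrics to intervention participants.

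Under Study Aim 2, the Data Analytic Plan models HbA1c by LMM and applies the same strategy to the remaining physiological and psychosocial outcomes, comparing the two arms. Normalizing transformations are tried first. If none works, "we will, instead, apply a generalized linear mixed model with a link function appropriate to the distribution of the outcome measure". The plan names where it expects this: "as is likely to be the case for the time in range, below range, and above range variables as well as the counts of". The sentence goes on to name clinical events of both kinds, low and high glucose.

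The closing paragraph of the same section begins "Finally, we use results of LMM analyses for the following". The first use listed is Cohen d and eta-squared, promised "for the intervention versus control condition on each of the physiological and psychosocial outcome measures". No other effect measure is named for outcomes that leave the LMM.

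**The concern.** Two adjacent parts of the plan do not fit together. One expects seven listed outcomes to be analysed by something other than an LMM. The other requires LMM-based standardized effects, between arms, for every outcome. For three of those seven there is a harder obstacle, since the control arm supplies no data.

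The plan says that effect estimation, rather than testing, is the focus of Aim 2, and that the resulting statistics will help to design the full-scale trial. If the rule is followed literally, the CGM rows of the effect-size table cannot be filled. The event-count rows would hold a number that mixes the relative effect with the background event rate. Sizing a later trial on a count endpoint needs event rates and dispersion, and d supplies neither.

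**Working it through.** The plan gives no figure to reproduce here. The check is a count of outcomes, a comparison of what the plan says about each, and an illustration for the counts.

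**Step 1. Count the physiological outcomes** (Table 4 and Secondary Outcomes).
- HbA1c: 1
- Time in, below and above range: 3
- Event counts: 2 causes × 2 settings = 4
- Total: 1 + 3 + 4 = 8

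If the ED and hospitalization item is read as a single outcome, as the Secondary Outcomes sentence allows, the total is 1 + 3 + 1 = 5.

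**Step 2. Set each group against the promise.**

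| Outcome group | Control-arm data? | Model the plan expects | Between-arm d and eta-squared from LMM? |
|---|---|---|---|
| HbA1c (1) | Yes | LMM | Yes |
| CGM range metrics (3) | No | Probably generalized | Impossible under any model |
| Event counts (4) | Yes | Probably generalized | Not directly |
| Psychosocial scales | Yes | LMM by default | Yes |

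Three of the eight physiological outcomes cannot meet the promise. Four more probably do not fit it. One is unaffected, as are the psychosocial measures (depression, quality of life, social support, interpersonal processes of care), which are not on the plan's list of likely departures.

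**Step 3. Why the counts fit poorly.** A model with a log link estimates a rate ratio. It has no single residual SD on the outcome scale to divide by, and no sum-of-squares split from which to form eta-squared.

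As an illustration, take Poisson counts in two equal arms with control rate λ0 and intervention rate λ1 = 0.5 λ0. The documents give no event rates, so both the rate ratio of 0.5 and the range of λ0 are assumptions.

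- d = (λ0 − λ1) / √[(λ0 + λ1)/2]
- eta-squared = d² / (d² + 4)

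| λ0 per 3 months | λ1 | d | eta-squared |
|---|---|---|---|
| 0.05 | 0.025 | 0.025/√0.0375 = 0.13 | 0.004 |
| 0.1 | 0.05 | 0.05/√0.075 = 0.18 | 0.008 |
| 0.3 | 0.15 | 0.15/√0.225 = 0.32 | 0.024 |
| 1.0 | 0.5 | 0.5/√0.75 = 0.58 | 0.077 |

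The rate ratio is the same in every row, yet d varies by a factor of about 4.5 (0.577/0.129), because the SD of a count moves with its mean. With overdispersion (variance = mean + 2 × mean², also assumed), d runs from 0.12 to 0.35 over the same rates. So d depends on dispersion as well.

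**The case against.** The strongest reply is that LMM in the closing paragraph is shorthand for the mixed-model analyses as a whole. The abstract names linear and generalized linear mixed models together, and the plan introduces the generalized model as a branch of its LMM work. What remains would then be an unnamed effect measure, which a condensed article may leave to the analysis plan. This reading is plausible, but it does not rescue the text. The article does name the measures and their scope: d and eta-squared, between arms, on each outcome. No reading of LMM creates control-arm CGM data, and d and eta-squared are not direct products of a generalized model with a non-identity link.

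Several limits on the point do stand:
- The move to a generalized model is conditional. Transformations come first, and the plan says only that failure is likely.
- No link function is fixed.
- A d can be obtained for counts from raw means and SDs or by a latent-scale conversion, though the plan describes neither. A reader might infer that standardized effects never apply to such outcomes, and that goes too far.
- A reader might also infer that the promise can be kept for only one outcome in eight. That tally leaves out the psychosocial scales, which the same promise covers and which stay in the LMM by default.
- It is tempting to call a d for the counts useless because events will be sparse and a few participants would set the SD. The documents give no event rates, so this cannot be shown.
- The plan already describes these statistics as less than definitive because the sample is small.

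**Conclusion.** The point holds with limited scope. For the three CGM range metrics the stated rule cannot be carried out, and this rests on no assumption beyond the documents. For the four event counts (or the one combined event outcome) the rule does not fit the model that the plan itself expects to use. That part depends on the expected departure from normality actually occurring. The illustrated range of d, 0.13 to 0.58 at a constant rate ratio, rests on assumed Poisson rates. It shows dependence on the base rate, not that d has no meaning. HbA1c and, by default, the psychosocial scales are untouched.

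The documents do not support abandoning eta-squared everywhere, since it remains available wherever an LMM is fitted. This is a minor, inexpensive correction to a feasibility pilot and does not threaten its primary aim.

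**What to change.** Under Study Aim 2 of the Data Analytic Plan:
- Restrict Cohen d and eta-squared to outcomes actually fitted by LMM. Dropping eta-squared altogether is optional.
- For the four event counts, report rate ratios and absolute rates per person-3 months in each arm, with 95% confidence intervals. Add the observed event rates and dispersion for planning the full-scale trial.
- Describe time in, below and above range within the intervention arm only, and remove these metrics from the between-arm contrasts and the effect-size list.

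This changes wording only and needs no new data. The cost is that effects can no longer all be lined up on one common metric.
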